| Aerobic capacity test (VO 2 peak graded stress test) | Baseline; 4 months; 1 year                                         | 30-60 minutes total, dependent on individual capacity                      |
| Physical activity monitoring                                    | 1 week after each testing time-point                               | Actiwatch monitors worn for a duration of 1 week                           |
| Sleep monitoring                                                | 1 week after each testing time-point, as well as prior to Baseline | 7-day Sleep Diary and sleep questionnaire (completed at home)              |
| Dietary intake assessment                                       | 1 week after each testing time-point                               | 3-day food diary recorded with Research Food Diary app (completed at home) |
| Gut microbiome                                                  | Baseline; 4 months; 1 year                                         | 1 sample (completed at home)                                               |

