## **IX. Physical activity monitoring**

Physical activity and energy expenditure will be monitored by an Actiwatch Spectrum Plus (Koninklijke Philips, Amsterdam, Netherlands). The Actiwatch is a small, unobtrusive electronic physical activity monitor on an adjustable wrist strap that is worn on the left wrist. If participants have left-arm paresis the monitor will be fitted to the right wrist. Participants will be asked to wear the waterproof Actiwatch 24 hours per day for 7 days. In previous studies, conducted by the current Investigators, involving the use of Actiwatches for the duration specified there have been no complaints or concerns raised by participants.

The Actiwatch will be fitted onto participants at each of the three timepoints throughout the study, after the MRI scan and cognitive testing has been completed. Following the 7 day monitoring period, participants will be asked to return the de-identified Actiwatch in a de-identified pre-paid envelope to the study investigators.

In addition, participants will be asked to keep a daily activity diary that records participant activity levels between assessment visits. Such diaries are common place as a part of general post-stroke rehabilitation programmes and this is not expected to be an inconvenience for participants.

Time spent active will be used as a co-variate for data analysis.

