## **X. Sleep monitoring**

The Actiwatch Spectrum Plus (Koninklijke Philips, Amsterdam, Netherlands) has the capacity to record objective sleep activity, therefore two measures will be used to track subjective assessment of sleep during the same three time-points as the Actiwatch use (as above).

Use of a Sleep Diary is common practice in sleep research during the period of wearable sleep trackers (such as the Actiwatch) in order to corroborate objective measures of sleep. Therefore, an adapted Sleep Diary from the widely used Core Consensus Sleep Diary [39] will be used during the one week of Actiwatches to capture subjective bedtime, sleep time, nighttime awakenings, and morning rise time. 2. The Pittsburgh Sleep Quality Index (PSQI) [40] questionnaire is a retrospective self-report 10-item questionnaire that invites participants to rate their sleep quality and sleep disturbances over a one-month period. The PSQI yields a global score of sleep quality across seven domains: subjective sleep quality, sleep onset latency, sleep duration, sleep efficiency, sleep disturbances, use of sleeping medications, and daytime dysfunction, with a global score of >5 indicating poor sleep. The PSQI is considered the standard subjective sleep questionnaire and widely used and validated within the research community, found to have high internal consistency and used with both older adults and stroke patients [27, 41, 42].

The Sleep Diary and sleep questionnaire will be returned with the Actiwatch at each assessment. Completion time for both the subjective measures of sleep is expected to take between 10-30 minutes (in total), per each assessment time-point.

Changes in sleep (e.g., significantly increased or decreased total sleep time, increased sleep onset latency, decreased sleep efficiency, increased wake after sleep onset) will be used in analyses as a moderator for improvement in brain health.

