#### c. STATISTICAL METHODS TO BE UNDERTAKEN

The analysis can be considered in 3 parts, aligned with primary and secondary hypotheses:

- i. **Primary outcome and hypothesis: Comparing brain volumes between stroke participant groups:** Primary outcome will be analysed on an intention to treat basis, The difference in brain volume from baseline to 4 months will be analysed using an ANCOVA model with exercise intervention group as a factor (e.g., Physical fitness training vs. Balance training groups), with baseline brain volume and functional status as co-variants (dichotomised as mRS = 0-1, 2 and 3).
- ii. **Secondary outcome and hypotheses: Correlating brain volume with blood pressure control and incident stroke:** Secondary outcomes will be analysed using appropriate repeated measures random effect logistic regression models with dichotomised hypertension status or silent/recurrent brain infarction (as defined in methods) as dependent variables, treatment group as independent variable, and functional status dichotomized as a covariate (as above). The initial regressive analysis will examine the

differences between participants with good and poor blood pressure control, using this as a binary measure. The presence of incident subclinical stroke will also be included as a binary variable. In the regional volumetric analyses, total brain volume, regional white matter, cortical and subcortical grey matter volume changes will be modelled using this design.

- iii. **Exploratory analyses: Independent effects of exercise on blood pressure, incident stroke, diastolic cardiac indices, and aerobic capacity:** Exercise effects on end-organ function and fitness (i.e., aerobic capacity) are likely dissociable, however emphasise that this component is exploratory. For the purposes of these analyses, we define each of our end-organ metrics as: brain volume, cognitive function, incident stroke, diastolic cardiac indices, aerobic capacity (VO2max), sleep duration, onset latency, bedtime/rise time variability (minutes), and sleep efficiency (%). Exploratory analysis will be conducted using appropriate regression models to investigate the associations between BP, incident stroke, diastolic cardiac indices, aerobic capacity. In addition, mediation analyses will be conducted to explore the possible mediating role of sleep in preservation of brain volume.

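### Section 5.d.X makes change in sleep, a post-randomisation variable, a moderator while 8.c(iii) makes sleep a mediator, and same-visit sleep and MRI data cannot show which affects which (minor)

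*Protocol*

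**What the plan says.** **Role of sleep.** Protocol 8.c(iii) plans that "mediation analyses will be conducted to explore the possible mediating role of sleep in preservation of brain volume". Section 5.d.X says that changes in sleep, such as altered total sleep time or efficiency, "will be used in analyses as a moderator for improvement in brain health". The lay summary (3.a) also calls the role moderating. The sleep background in 3.c leaves it open between moderator and mediator.

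**Timing.** Section 5.d.IX has the Actiwatch "fitted onto participants at each of the three timepoints throughout the study, after the MRI scan and cognitive testing has been completed", then worn for seven days. Under 5.d.X the sleep diary "will be used during the one week of Actiwatches to capture subjective bedtime" and related times. The procedures table in 5.b schedules sleep monitoring "1 week after each testing time-point, as well as prior to Baseline". The Pittsburgh Sleep Quality Index (PSQI) asks participants to "rate their sleep quality and sleep disturbances over a one-month period".

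**Status.** Section 8.c(iii) stresses its own limits: "however emphasise that this component is exploratory". It does not say which sleep measurement is paired with which scan.

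**The concern.** There are two separate problems.

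1. **Moderator.** Asking for whom exercise works better needs a characteristic that allocation cannot have changed. Change in sleep from baseline fails that condition. If exercise alters the level or spread of sleep change, an interaction with it can appear without any true effect modification.

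2. **Mediator.** The pathway of interest runs from exercise to sleep to brain volume. If 4-month device or diary sleep is paired with 4-month volume, the mediator is recorded after the outcome it is meant to explain. A mediation model then shows that group, volume and sleep are related. It gives the same positive answer when volume affects sleep and sleep does nothing to volume.

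At stake is a mechanism statement in a secondary report, not the comparison of the two arms.

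**Working it through.** **1. Order of measurements**

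| Sleep source | When recorded | Relative to the 4-month MRI |
|---|---|---|
| Diary and questionnaire before Baseline (5.b) | before randomisation | before, but cannot be a post-randomisation mediator |
| Actiwatch and diary, baseline week | after the baseline MRI | before; the protocol does not say whether the week ends before allocation |
| Actiwatch and diary, 4-month week | after the 4-month MRI | **after** |
| PSQI at 4 months | one-month look-back | mostly before |
| Actiwatch and diary, 12-month week | after the 12-month MRI | after |

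No Actiwatch or diary recording is scheduled between the baseline week and the 4-month visit. The 4-month recording does precede the 12-month MRI.

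**2. Size of the same-visit problem**

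Inputs from protocol 8.b: two-sided alpha 0.05, d = 0.6, 120 recruited, 30% attrition. So 120 × 0.7 = 84 evaluable, or 42 per arm. Assumed, because the documents give no figure: the sleep-volume correlation r.

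Model in which sleep has no effect on volume, with G for group:
- V = 0.6·G + e₁
- S = r·V + √(1 − r²)·e₂

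Mediation is declared if the group term in S ~ G and the sleep term in V ~ G + S are both significant.

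Expected false indirect effect: the group-to-sleep path is r·d and the sleep-to-volume path is r, so the product is r²·d, a share r² of the total effect.
- r = 0.3: 0.09 × 0.6 = 0.054, or 9% of the total
- r = 0.5: 0.25 × 0.6 = 0.15, or 25% of the total

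Rejection rates, 4,000 simulated trials per cell:

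| r | 42 per arm | 60 per arm |
|---|---|---|
| 0 | 0.2% | 0.3% |
| 0.2 | 3.8% | 6.1% |
| 0.3 | 9.6% | 15.2% |
| 0.5 | 26.7% | 37.8% |

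With d = 0.3 the rate at 42 per arm is 5–13% for r from 0.3 to 0.6. With d = 0 it stays at or below about 5%.

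**3. Size of the moderator problem**

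Model with no true moderation, where U is underlying sleep and k is extra spread in the exercise arm:
- V = 0.6·G + r·U + e
- S = U + 0.5·G + k·G·noise

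The slope of V on S is r in the balance arm and r/(1 + k²) in the exercise arm. With k = 1 (exercise doubles the variance of sleep change, an assumption) the false interaction is r/2 − r = −r/2, that is −0.15 at r = 0.3 and −0.25 at r = 0.5. At 42 per arm the interaction test rejects in 12–30% of trials for r from 0.3 to 0.5. With k = 0 it rejects in about 5%.

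**4. The lagged alternative**

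Take sleep at 4 months as mediator and 12-month volume as outcome, adjusted for 4-month volume, with V₁₂ = 0.9·V₄ + 0.5·e.
- Reverse causation only (d = 0.6, r = 0.5): false mediation in under 2% of trials. With imperfectly measured volume (assumed reliability 0.8 or 0.6) this becomes about 5% or 9%.
- True mediation during the 8-week programme (assumed group-to-sleep 0.6, sleep-to-volume 0.5, 42 per arm): the same-visit test detects it in about 76% of trials, the lagged test in about 4%.

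The lagged test guards against reverse causation but cannot see mediation in the period that the primary hypothesis concerns.

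**The case against.** The strongest defence is that 8.c(iii) names no time-points. Secondary hypothesis iii links sleep to brain volume at both 4 months and 1 year, so a correctly ordered pairing is available, and details of an exploratory mediation model are commonly left to an SAP. This stands: the protocol does not commit to a reversed test, and a reader who inferred that it does would go beyond the text.

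A reader might also infer that every sleep recording follows the scan it would explain. The documents do not support that. Monitoring is scheduled before Baseline, and the PSQI looks back a month. Three of the four sleep metrics in 8.c(iii) (duration, onset latency, efficiency) are also PSQI domains. Neither exception makes same-visit device or diary data informative about direction.

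It is fair to add that moving the device week to just before the MRI would leave much of the ambiguity, because near-simultaneous measurements carry little information on direction. That argues for cautious reporting rather than a changed schedule.

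Finally, 5.d.X speaks of moderating improvement in brain health and does not specify a treatment-by-sleep interaction, so the interaction model above is an illustration. The conflict of roles between 5.d.X and 8.c(iii) remains however the term is read.

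**Conclusion.** The point holds and is minor. Section 5.d.X gives a moderator role to a post-randomisation variable that 8.c(iii) would treat as a mediator. Any same-visit pairing of Actiwatch or diary sleep with brain volume leaves the direction of effect open. These are two separate defects; the moderator wording does not cause the reverse-causation problem.

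The error rates (about 10% at r = 0.3 and 26% at r = 0.5 for mediation; 12–30% for the interaction) depend on assumed correlations, a true d of 0.6 for the mediation figures, and an assumed doubling of variance for the interaction. They show what could happen, not what to expect. Nothing here touches the ANCOVA on 4-month brain volume or the trial's main conclusion.

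**What to change.** 1. **Section 5.d.X:** use pre-randomisation sleep as the moderator, taken from the diary and questionnaire that the 5.b table schedules before Baseline. Section 5.d.X currently mentions only the three visit time-points, so carry that recording across. Treat change in sleep only as a candidate mediator, in line with 8.c(iii).
2. **Section 8.c(iii):** state that mediation results from same-visit sleep and volume are reported as associations with direction not established.
3. **Section 8.c(iii), added sensitivity analysis, not a replacement:** relate baseline-to-4-month change in sleep to 12-month brain volume, adjusted for baseline and 4-month volume, age and mRS group. State that it addresses only volume change after 4 months and cannot detect mediation during the 8-week programme.

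The cost is wording; every measurement is already scheduled. The sensitivity analysis relies on 12-month scans, where more attrition is to be expected than at 4 months.

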#### d. QUALITATIVE ANALYSIS

##### **Data management**

NVivo 10 software (or similar) will be used to assist data management. Digitally recorded interviews will be professionally transcribed verbatim and checked against the recordings and corrected for accuracy. Prior to analysis, all transcribed information that may identify an individual or a hospital (for example names will be replaced with assigned codes).

##### **Data analysis**

Qualitative descriptive content analysis will use a six step strategy [44] including: identifying and coding all meaningful text units from interview data and field notes; recording insights and reflections on the data; sorting the data to identify similar features, phrases, concepts; constant comparison to look for commonalities and differences among the data; deciding on generalisations or themes that hold true for the data and/or for particular participant sub-groups.

To enhance trustworthiness of the findings, this analytical process will be undertaken by two researchers who will familiarise themselves with the data through repeated reading of the transcripts and will undertake the coding step independently. For the latter iterative steps of analysis the researchers will work collaboratively using discussion to reach consensus.

Thematic saturation for a particular subgroup will provide confidence that our data is representative, and will be considered to have occurred if no new themes emerge in the final three interviews analysed.

## 9. STORAGE OF BLOOD, TISSUE AND STOOL SAMPLES

### a. DETAILS OF WHERE SAMPLES WILL BE STORED, AND THE TYPE OF CONSENT FOR FUTURE USE OF SAMPLES

Participants will be asked to provide 10ml of venous blood at their first, second, or third visit for APOE genotyping and analysis of other genetic and blood markers. They will provide an additional 27ml of venous blood at each study visit. Each sample will be assigned a unique identifier and will be locked in a storage freezer.

Participants will be asked to provide a stool sample at the 2-, 4-, and 12-month timepoints for the purpose of analysing the gut microbiome. Each sample will be assigned a unique identifier and will be locked in a storage freezer.

Consent will be obtained separately for blood and stool samples – that is, participants can refuse to provide either or both of the samples, and still take part in the study. Samples will be stored for future genetic or biomarker analyses for 10 years. After this time, they will be destroyed as per department protocol for human samples. If participants decline to consent for use in future research, the sample will be disposed of after a year following completion of the research.

## 10. DATA SECURITY & HANDLING

### a. DATA COLLECTION

A Case Report Form (CRF) will be completed for each study participant summarising all clinical screening and study data. Participants will only be referred to in the CRF by their numerical identifier in order to retain confidentiality. All data entered on the CRF will have supporting source data located at the study site in the participant's medical record.

### b. DETAILS OF WHERE RECORDS WILL BE KEPT & HOW LONG WILL THEY BE STORED

*ANY IDENTIFIABLE DOCUMENTS WILL BE KEPT FOR 7 YEARS IN PROF [name]'S LOCKED OFFICE IN A LOCKED BUILDING (I.E., ALFRED CENTRE, MONASH UNIVERSITY) OR IN AN UNMARKED LOCKED FILING CABINET ON THE FOURTH FLOOR OF THE AIMSS FACILITY(FOR WESTERN HEALTH PARTICIPANTS). AFTER THIS TIME, PAPER COPIES WILL BE SHREDDED AND DISPOSED IN CONFIDENTIAL DOCUMENT PAPER RECYCLING. COMPUTER DISCS WILL BE ERASED, ALONG WITH BACK UP FOLDERS (HARD-DRIVES).* CONFIDENTIALITY AND SECURITY

The investigators intend to protect participants' anonymity and the confidentiality to the fullest possible extent, within the limits of the law. Each participant will be assigned a numerical identifier and their name and contact details will be kept in a separate file from any data that they supply. In any publication and/or presentation arising from this research project, information will be provided in such a way that the participant cannot be identified. Data will be presented and discussed in terms of participant groups, not individual participants.

### d. ANCILLARY DATA

MRI scans, if used in publications, will have all text details removed and consist of brain images only. It should be noted that all images acquired on the 3T BRI Siemens scanner contain no identifiable information, as they are produced in DICOM format which only allows the image file. Staff will assign each participant a unique numerical identifier, and only this is tagged to the participant's file, but is not present on any image once converted into a viewable mode. Scans will be kept on password-protected server, separate to any cognitive data that participants provide. No films will be printed. Scans will be stored on the server for 7 years, after which time they will be deleted.

Voice recordings as a part of the qualitative interview will also be kept on a password-protected server, denoted only by participant number, and separate to any other participant information.

